#### Quasi-experimental design

We will conduct a cross-sectional household survey to collect quantitative data to measure knowledge, attitudes, practices, and uptake of ASRH services. The indicator used to compute the sample size was the FP services utilization rate among adolescents aged 15–19 years, using the most current data from the study areas obtained from the Kenya health information system. The FP utilization for both groups was computed and the lowest prevalence of the two was used in computing the sample size to guarantee the maximum possible sample size. An intra-class correlation of 0.03 was assumed resulting in a design effect of 1.87. The study is powered to detect a 15-percentage point difference between the two groups in each county, 95% confidence interval, with power of 80%. Furthermore, we account for a 10% loss due to possible non-responses and incomplete data. Using the parameters described, the sample size was determined to be 264 per arm (total 528) and 231 per arm (total 462) per arm in Kisumu and Kakamega counties, respectively, at each data collection period. A sample size of 990 participants will therefore be interviewed at baseline, and a similar number at endline. Community units are made up of villages, which, for the purpose of sampling, will be “cluster units.” Since the total number of units in each cluster unit and ward is known, villages will be randomly selected; eight villages in Kobura ward and eight from Kajulu ward in Kisumu County. In Kakamega, seven villages in Kholera ward and seven villages in Bunyala West ward. The sample size will be equally distributed among the selected villages in each ward. Households will be selected through systematic random sampling at an interval of 100–200 m from a particular landmark, until the required sample size is achieved for each ward. In households with multiple adolescents, the Kish method will be used to randomly select one individual from each household [10].

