### Data analysis

Data from in-depth interviews, FGDs, and key informant interviews will be transcribed, translated, and back translated then entered in qualitative data software (Atlas ti.8). We will then develop a coding frame using a grounded theoretical framework. Independent analysis will be conducted by different analysts and subsequent comparison between the developed coding matrices will be used to develop a reliability factor for the analysis. The trends from the emerging themes will be iteratively developed by repeatedly analyzing data collected at different time points. Verbatim generated alongside the code matrix will be used to support the emerging thematic framework.

Descriptive analysis of quantitative variables will be done using measures of central tendency (mean, median) and measures of dispersion (range, standard deviation), as appropriate. The inter cluster correlation will be computed. We will then conduct an exploratory analysis to compare outcomes by the sociodemographic, cultural, and economic characteristics (age, education, religion, marital status, life skills, wealth quintile, place of residence [urban or rural]) using the Rao-Scott chi-square test to see if there is any association. To determine the relative importance of these factors on the outcomes, generalized estimating equations, univariate, and multivariate logistic regressions will be used to adjust for clustering within the clusters. Results from the regression analysis will be reported as odds ratio and 95% confidence intervals.

For the quasi-experimental design, our hypothesis is that adolescent girls in the intervention study arm will have greater increases in FP utilization and improved knowledge and attitudes than girls in the control arm. We will estimate the intervention effect by subtracting the baseline FP utilization rate from the estimates at endline then calculating the difference between the comparison and intervention sub-counties (the difference-in-difference analysis). The difference-in-differences analysis assumes a common trend in the outcome in both the intervention and comparison area. We will measure potential confounders at baseline and endline and adjust our analysis for any compositional changes over time in these confounders. All statistical analysis will be considered statistically significant for *p*-values less than 0.05.

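### The 80% power stated for each county makes no allowance for having only 8 or 7 villages per arm; with a village-level t reference it is about 73–79%

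*Protocol article*

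**What the plan says.** All the sample-size inputs are in the Quasi-experimental design paragraph under Sampling.

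- **Target:** "The study is powered to detect a 15-percentage point difference between the two groups in each county, 95% confidence interval, with power of 80" per cent.
- **Clustering:** "An intra-class correlation of 0.03 was assumed resulting in a design effect of 1.87".
- **Losses:** "we account for a 10% loss due to possible non-responses and incomplete data".
- **Sizes:** 264 per arm in Kisumu and 231 per arm in Kakamega at each survey round, shared equally among the villages chosen in each ward.
- **Villages:** "eight villages in Kobura ward and eight from Kajulu ward in Kisumu County", and "seven villages in Kholera ward and seven villages in Bunyala West ward".

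The planning family-planning (FP) utilization rate comes from the Kenya health information system and is not printed.

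Under Data analysis, the methods named for clustered data are the Rao-Scott chi-square test and "generalized estimating equations, univariate, and multivariate logistic regressions". Both serve the analysis of sociodemographic and other factors. The primary difference-in-differences is in a separate paragraph, with no test or standard error stated. The significance level is 0.05 throughout ("All statistical analysis will be considered statistically significant for" p below 0.05).

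**The concern.** The power claim is made separately for each county, and each county has few villages. Multiplying a simple-random-sample size by a design effect treats the clustered variance as known and keeps the normal critical value of 1.96. In practice the variance must be estimated from 16 or 14 village values, and a comparison that respects this needs a larger critical value. If the 5% level is held, power falls below the stated figure. If 1.96 is kept with an estimated variance, the 5% level is not held. The per-county statement therefore promises somewhat more than the design delivers. This is so on the plan's own two-group comparison, before the difference-in-differences or the restriction to sexually active girls is considered.

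**Working it through.** **1. Reproduce the plan's sizes.** Design effect = 1 + (m − 1) × 0.03 = 1.87 gives m = 30 analysed girls per village. Then:

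- Kisumu: 8 × 30 = 240 completes; 240 × 1.1 = 264.
- Kakamega: 7 × 30 = 210 completes; 210 × 1.1 = 231.

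Both match the article exactly. Dividing by the design effect gives 240/1.87 = 128.3 and 210/1.87 = 112.3 per arm. The ordinary two-proportion formula (two-sided 5%, 80% power, 15-point difference) returns these sizes for some low planning rate:

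- unpooled variance: about 17.9% (Kisumu) and 13.6% (Kakamega);
- pooled variance: about 17% and 12.8–12.9%.

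These rates are back-solved, not stated in the article.

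**2. Replace the normal reference by t.** If normal-theory power is exactly 80%, the non-centrality is 1.960 + 0.842 = 2.80, whatever the planning rate. With k villages per arm, a village-level comparison within one county has 2(k − 1) degrees of freedom. Power is P(|T| > t_crit), with T noncentral t.

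| | Kisumu (k = 8) | Kakamega (k = 7) |
|---|---|---|
| Degrees of freedom | 14 | 12 |
| Critical value (normal: 1.960) | 2.145 | 2.179 |
| Power, 80% met exactly | 74.1% | 73.0% |
| Power, sizes from pooled-variance formula (non-centrality 2.83, 2.84) | 75.0% | 74.0% |
| Power, sizes from continuity-corrected formula | 78.9% | 78.6% |
| Power, rounded up by as much as a whole village per arm (2.80 × √(8/7) = 3.00; 2.80 × √(7/6) = 3.03) | 79.5% | 79.3% |

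**3. Check by simulation.** Beta-binomial data were generated with intra-class correlation 0.03, 30 girls per village and control rates of 16.9% and 12.75%. The village-level t-test had power 75.2% and 74.3%, with type I error 4.9% in both counties.

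**4. Detectable difference.** With the t reference, 80% power needs a non-centrality of 3.01 (14 df) or 3.05 (12 df). Write p for the control rate, Δ for the difference and n for completes per arm (240, 210). Solving Δ / √{[p(1 − p) + (p + Δ)(1 − p − Δ)] × 1.87 / n} for these values, at the unpooled back-solved rates, gives Δ = 16.2 points (Kisumu) and 16.5 points (Kakamega), against 15. These are upper values; any rounding up of the sizes would bring them closer to 15.

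**5. Conditional type I error.** Suppose a per-county contrast were tested by generalized estimating equations (GEE) with an uncorrected sandwich variance and normal quantiles. With equal village sizes, that variance is (k − 1)/k times the unbiased one. Type I error is then P(|t| > 1.96 × √((k − 1)/k)): P(|t₁₄| > 1.833) = 8.8% and P(|t₁₂| > 1.815) = 9.5%. Simulation gave 8.6% and 9.6%.

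**The case against.** **The arithmetic is not wrong in itself.** The sizes reproduce, and a design effect with normal quantiles is a common large-sample approach. That stands. The point concerns the power claimed from it when a county has 16 or 14 villages.

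**The shortfall may be small.** The planning rate is not printed, and 264 and 231 are exactly what rounding up to whole villages would give. Power could then be as high as about 79%. A reader might take 74% and 73% as the true figures, but the document supports only a range. Even its top stays below 80%, and the article mentions neither rounding nor a continuity correction.

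**No analysis that rejects too often is planned.** A reader might infer that the primary test will have a 9% type I error. The article does not say so. GEE is named for the factor analysis, alongside Rao-Scott, and no test is given for the difference-in-differences. A small-sample correction may be in the analysis plan, which is not shown. The 9% is therefore only a warning. Such a correction would remove that risk but would not restore the power; it would bring in the t reference used above.

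**A pooled analysis is better placed.** With 15 villages per arm over both counties, the same endline comparison would have about 97% power, and the uncorrected robust test a type I error of about 7%. That is correct, and the shortfall should not be read as applying to a pooled comparison. It does not rescue a sentence that claims 80% in each county.

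**Villages may not be the only level of clustering.** Each county has one intervention and one control ward, so degrees of freedom counted on villages ignore ward-level variation. The t reference is used here within the plan's own framework, which treats villages as the clusters. It is not shown to be valid against differences between wards.

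**Conclusion.** The concern holds as an overstatement of per-county power. For the two-group comparison that the article powers, power with a village-level t reference is about 74% (Kisumu) and 73% (Kakamega) if normal-theory power was exactly 80%. It is about 75% and 74% under a pooled-variance formula, and at most about 79% if sizes were rounded up to whole villages. The overstatement is therefore about 1 to 7 percentage points.

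This rests on the stated intra-class correlation of 0.03, 30 completes per village, equal village sizes and villages as the only clusters. The 74% and 73% need no planning rate; the detectable differences do, and they use back-solved values. The document does not establish an inflated type I error for the primary analysis.

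**What to change.** In the Quasi-experimental design paragraph, restate the per-county power as about 73–79%, narrowed to about 74% (Kisumu) and 73% (Kakamega) if no rounding up was done. Alternatively, keep 80% and give the detectable difference as up to about 16.2 and 16.5 points. Printing the planning FP rate and the formula used would replace the range with one figure per county.

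Base the per-county contrast on a small-sample method: a t-test on village-level values, or GEE with a bias-corrected sandwich variance and t quantiles on (villages − 2) degrees of freedom. If the analysis plan already does this, a cross-reference is enough.

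The cost is a change of wording and a slightly less favourable stated power. No more participants are needed.

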### Study eligibility criteria

Adolescent boys and girls aged 15–19 years:

• Living, at the time of the survey, in the study sites

• Voluntarily provides informed consent (emancipated minors/adolescents aged 18 and 19 years)

• Voluntarily provides assent coupled with parental permission for minors

### Study implementation

The study is designed to employ two design methods: a cross-sectional formative assessment (Phase 1) and a quasi-experimental study design (Phase 2).

#### Phase 1: formative assessment

A qualitative cross-sectional study design will be utilized for the formative assessment to establish the barriers, preferences, and experiences of adolescents while seeking and using ASRH only. In addition, a pre-intervention and post-intervention client exit interviews will be conducted with both boys and girls receiving ASRH services in health facilities and outreach camps in the intervention and control arms. The aim of the client exit interview will be to establish the quality of ASRH services offered at facilities and outreach points. Information gathered in both formative assessments will be used to develop interventions that will improve access to and quality of ASRH services.

#### Phase 2: quasi-experimental design

A quasi-experimental evaluation design is proposed to evaluate the rollout of the ASRH program intervention to determine the effectiveness of a combined model to improve utilization of ASRH services. In both counties, program intervention and comparison groups will be selected, while taking measures to ensure that the comparison group matches the program intervention group in general composition, such as possession of similar sociodemographic characteristics. Using the stratified cluster sampling approach, a pre-intervention and post-intervention household survey will be conducted in the two study arms targeting adolescent girls at baseline and endline. The aim of the survey will be to establish the status of adolescents’ knowledge, attitude, and utilization of ASRH services, primarily FP. Implementation of the program intervention will be population-based, targeting adolescent boys and girls aged 15–19 years in the intervention areas. An analysis of the primary outcome (utilization of FP services) will be undertaken to establish the difference in difference between the control and intervention arm, before the intervention (using the baseline survey data) and after the intervention (using the endline survey data).

### Description of intervention

The ASRH service package, which will target both boys and girls, will include provision of ASRH services, including counselling and age-appropriate, comprehensive sexual education for behavior change using a multi-sectoral approach with an aim to increase utilization of ASRH services. The intervention will be anchored on the findings of the formative assessment that will seek to explore the ASRH context in the intervention wards. In the comparison group, adolescents will continue to receive the routine ASRH activities provided at facility level. Health facility data quality improvement processes will be implemented in both groups to ensure that ASRH activities are accurately documented. Standard ASRH interventions to be provided are those approved by Ministry of Health and include FP counselling, information and services, HIV counselling, testing and treatment, and screening and treatment for sexually transmitted infections (STIs). The conceptual framework for these interventions is outlined in Fig. 1.

**Fig. 1 Fig1:**
[figure not shown]
Conceptual framework

The quality of ASRH services at health facilities at endline will also be assessed through client exit interviews. ASRH service implementation will be through three platforms.

**The community-based component** will involve community health workers and other relevant Community Own Resource Persons (CORPs), such as adolescent counsellors and peer educators, who will be oriented on adolescent-friendly services and other innovative facilitation techniques, such as Education through Listening and Counselling for Choice. The community health workers and CORPs will be supported to carry out household visits and small group sessions and to organize events targeting this cohort such as adolescent camps, symposia, dialogue days, thematic talks, sports days, and monthly facility open days where SRH topics shall be discussed. The sessions will use a targeted approach where services are designed and planned for adolescents alone, are offered in settings that meet the needs of the adolescents, and do not include other groups. During the monthly sessions, health workers will provide ASRH services to willing adolescents after comprehensive counselling. Community resources that are available for adolescents and that can positively contribute to their reproductive health—e.g., drop-in centers, sports facilities, social halls, and bursary funds—will be mapped by the study team led by the Ministry of Interior in collaboration with the Ministry of Health officials.

**The facility-based component** will involve orientation of health workers to provide adolescent-sensitive services. Health workers will be oriented on the values clarification and attitude transformation approach to remove barriers to ASRH services access stemming from misinformation, stigmatization, and negative attitudes toward adolescents seeking services.

**The school-based component** will entail engagement and advocacy sessions targeting the Ministry of Education and county leadership to create buy-in on ASRH rollout in schools. This is critical for schools to allow health workers to train teachers and students on ASRH, offer information, and refer students for services. Thereafter, the intervention schools will be mapped out and teachers trained on selected ASRH modules as recommended by national guidelines. The teachers will then carry out regular (weekly) ASRH sessions in schools and engage students in interactive challenges that build on the new knowledge and skills acquired through the ASRH sessions.

A social behavior change communication approach will be integrated across all service delivery points—i.e., in schools, facilities, and communities. ASRH interventions in schools will include sessions to engage students in interactive challenges that build on their new knowledge and skills acquired through the ASRH sessions. This can be through drama, club meetings, drama debate, music, and sports that will be organized using ASRH themes. Social behavior change communication at health facilities will include whole-site orientation targeting all workers within the participating facilities with information of the package of intervention. Services providers at these facilities will be oriented on recommended ASRH topics, transformation of attitudes, and the provision of adolescent-friendly services. Service providers will also be supported to carry out other interpersonal communication activities, such as facility open days for adolescents and formation of social support structures/groups for this cohort. Participating facilities will be assisted to draft a charter in support of adolescent-friendly services that will provide for, among other things, flexible hours to accommodate the timid, health-seeking behavior of adolescents.

**The virtual platform** is one of the approaches for delivery of ASRH services, but it is not included in this study as the study targets adolescents aged 15–19 years who are primarily in school, living in rural areas, and may not have access to technology platforms. The platform is likely to have more impact among the older youth (19–24 years).

In the comparison group, implementation of ASRH services will continue in the same manner as they are routinely or currently being implemented through health facilities. Health workers will be trained to provide adolescent-friendly services. An endline assessment will be done at the end of the 18 months’ implementation period. The table below presents a summary of the package of interventions that will be done in the two study arms.

The Table 2 presents a summary of the package of interventions that will be carried out in the two study arms.

**Table 2 Tab2:** Summary of package of activities by evaluation group

	Program intervention group	Comparison group
ASRH service delivery at facility level	✓	✓
ASRH service delivery at community level	✓	✗
ASRH service delivery in schools	✓	✗
Targeted social behavior change communication	✓	✗

### Study outcomes

Our primary outcome will be FP utilization among adolescents as defined as follows:

• *Number of sexually active girls reporting use of modern contraceptive methods*

• *Number of sexually active adolescents aged 15–19 years sampled*

Sexually active girls will be defined as those who report ever having sexual intercourse. Other secondary outcomes will be knowledge and attitude on the use of modern contraception, among others as outlined in Table 3.

**Table 3 Tab3:** Study outcomes

Other study outcomes among 15–19 years		
Knowledge	Attitude	Practice/utilization
Risks faced by adolescents in pregnancy/childbirth	Toward contraceptives	Utilization of FP services
Available methods of FP	Toward ASRH services offered in facilities/communities/schools	Sexual experience – delay in age at first sex
Secondary study outcomes among 15–19 years: Reduced teenage pregnancy rates in intervention group		

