### Study unit inclusion criteria and selection

Kisumu and Kakamega counties were selected as project areas in part because they are among the counties with the highest burden of teen pregnancy in Kenya—at 15 and 19%, respectively [9]. The study will focus on two sub-counties within Kisumu County (Nyando and Kisumu East) and two sub-counties within Kakamega County (Matungu and Navakholo). Within the identified four sub-counties, two wards have been selected in each sub-county, one as intervention (Kobura in Kisumu and Kholera in Kakamega) and the others as control (Bunyala West in Kisumu and Kajulu in Kakamega). The selection of the intervention ward is based on the poor reproductive and maternal health indicators coupled with low utilization of FP services among adolescents [9]. The wards were selected by the study team in collaboration with Ministry of Health officials after reviewing the wards’ service statistics. The intervention-comparison wards were selected to be similar with respect to sociodemographic characteristics and low utilization of FP services.

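### The primary rate is taken over girls who report ever having had sex, a group the programme can itself change, so part of a difference-in-difference could reflect who is counted rather than contraceptive uptake.

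*Protocol article*

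**What the plan says.** The Study outcomes section gives the numerator as "Number of sexually active girls reporting use of modern contraceptive methods" and the denominator as "Number of sexually active adolescents aged 15–19 years sampled". It then fixes membership: "Sexually active girls will be defined as those who report ever having sexual intercourse". There is no recall window.

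Table 3 in the same section lists "Sexual experience – delay in age at first sex" among the other study outcomes. The Description of intervention section describes the package as including "age-appropriate, comprehensive sexual education for behavior change using a multi-sectoral approach". Table 2 gives community delivery, school delivery and targeted behaviour-change communication to the intervention group only; facility-level delivery is in both groups.

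Under Quasi-experimental design, the surveys are cross-sectional with a similar number of girls at baseline and endline. The Data analysis section takes the difference-in-difference of the utilization rate and plans to adjust for compositional change in measured confounders. The Study population section says the household survey takes girls aged 15–19 without a first birth; it is not limited to girls who have had sex.

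**The concern.** The denominator at endline is measured after 18 months of a programme that one arm receives in full. If the programme delays first sex among girls who would not have used contraception, the rate rises with no extra user. If counselling makes non-users readier to say they have had sex, the rate falls although nobody has stopped. In both cases the endline and baseline rates describe differently selected groups, and the selection differs by arm.

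The planned safeguards do not reach this. Ever-sex status is not named as a confounder; it is a possible consequence of the programme. The common-trend assumption does not help either, because the shift would be caused by the intervention. What is at stake is whether a change in the primary rate can be read as a change in contraceptive uptake.

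**Working it through.** **1. The plan's own figures.** Design effect = 1 + (m − 1) × ICC. With ICC 0.03 and m = 30, this is 1 + 29 × 0.03 = 1.87, as stated. The cluster size fits: 264/1.1 = 240 = 8 × 30, and 231/1.1 = 210 = 7 × 30.

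**2. A plausible baseline rate.** The article states none. I back-solved it from a two-proportion sample size (difference 15 points, two-sided 5%, power 80%, no continuity correction), multiplied by 1.87 and 1.1.
- Kisumu: a rate near 17% needs n = 128, and 128 × 1.87 × 1.1 = 263.3, so 264. This matches.
- Kakamega: a rate near 13% needs n = 113, and 113 × 1.87 × 1.1 = 232.4, so 233, against 231 stated.
- With continuity correction the implied rates are about 13–14% and 9–10%.

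Mirror solutions near 68% and 72% also fit, but I set them aside because the article describes utilization as low. These rates are inferred. They also relate to a health-information-system indicator, which need not equal the survey rate among girls reporting sex. I therefore use 13%, 17% and, as a higher assumption, 30%.

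**3. Effect of the denominator alone.** Hold the number of users fixed and let only non-users enter or leave. If the denominator changes by a relative amount d, the new rate is r/(1 + d). The relative fall needed to gain 15 points is 1 − r/(r + 0.15).

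| Assumed use r | 10% fall | 15% fall | 25% fall | 15% rise | Fall needed for +15 points |
|---|---|---|---|---|---|
| 13% | 14.4% (+1.4) | 15.3% (+2.3) | 17.3% (+4.3) | 11.3% (−1.7) | 54% |
| 17% | 18.9% (+1.9) | 20.0% (+3.0) | 22.7% (+5.7) | 14.8% (−2.2) | 47% |
| 30% | 33.3% (+3.3) | 35.3% (+5.3) | 40.0% (+10.0) | 26.1% (−3.9) | 33% |

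**4. When users leave too.** Take 100 girls, 40 reporting sex, 12 users (30%), and let 10 leave the denominator. If all 10 are non-users, the rate is 12/30 = 40%. If they leave in proportion (3 users, 7 non-users), it is 9/30 = 30%, unchanged.

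**5. The all-girls rate.** With users fixed it is 12/100 throughout, by construction. It is not a neutral referee, however. Suppose delay cuts active girls from 40 to 32 and use among them rises to 35%. Users become 32 × 0.35 = 11.2. The primary rate rises 5 points, while the all-girls rate falls from 12% to 11.2%.

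**The case against.** The chosen denominator has a clear rationale: girls at risk of pregnancy are the ones for whom contraceptive use matters, and the Study population section ties the measure to primary prevention of pregnancy. Sexual experience is already a listed outcome, so some information on it is due to be reported. An extra analysis over all girls might also be in a fuller document that is not shown. This supports keeping the primary outcome. It does not remove the point, because the article itself fixes the denominator and gives no sign that the primary result will be read alongside a change in it.

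Several limits on size also stand. Ever having had sex cannot be undone, so true delay acts only through girls not yet active; changed reporting has no such limit. The table assumes that every girl who leaves is a non-user, which is the extreme case. Facility services run in both arms and comparison-arm health workers are also trained, so some influence on disclosure is shared. That the programme is open is an inference from its visible content; the article does not mention blinding.

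A reader might infer that a positive or null result would tell us nothing about uptake. The documents do not support that: at the rates the sample sizes imply, the full 15 points would need roughly half the girls reporting sex to disappear from the denominator. A reader might also want to require that the all-girls estimate point the same way before concluding an effect. Step 5 shows why that is unsafe: it could veto a programme that both delays sex and raises use among active girls.

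**Conclusion.** The concern holds as an interpretability weakness that is cheap to mend. The primary rate conditions on a status measured after the intervention and open to its influence, and the planned adjustment does not correct for this.

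The possible distortion is about +1.4 to +10 points for a 10% to 25% relative fall in girls reporting sex, and about −1.7 to −3.9 points for a 15% rise through non-users' disclosure. This assumes 13% to 30% baseline use and that only non-users move. At the back-solved rates of 13% to 17%, the upper end of the gain is 5.7 points. The direction cannot be settled in advance. Such a shift could blur a modest effect, but alone it is unlikely to account for the 15-point target.

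**What to change.** Keep the sexually-active rate as primary and pre-specify two results beside it:

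- the same difference-in-difference for modern-method use over all surveyed girls aged 15–19;
- the proportion reporting ever having had sex, by arm and round, with its own difference-in-difference.

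State that a primary effect will be read as increased contraceptive uptake only after both have been considered. Where the ever-sex share shifts differently between arms, report that the primary estimate may partly reflect a change in the denominator. Do not set a rule that the two estimates must agree in direction.

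The survey already samples girls regardless of sexual experience, so no new data are needed. The cost is the added analysis, some outcome wording and an all-girls effect that looks smaller in points. The additions do not correct misreported use: if existing users become readier to disclose, the all-girls rate rises as well. They also leave the restriction to girls without a first birth in place.
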